### **6.2.2.3 Risks Associated with Suboccipital Injection into the Cisterna Magna**

Risks associated with injection into the cisterna magna include local discomfort, CSF leakage resulting in headache, hematoma, meningitis, and puncture of neuronal tissue.

Intracisternal administration will be performed by an interventional radiologist or neurosurgeon who has experience with the procedure. Investigational product administration will be performed only after MRA and brain MRI confirm that there are no structural contraindications or blood vessels in the area of injection and that there is sufficient CSF space in the ICM to safely administer investigational product. The procedure will be performed with the patient under general anesthesia or deep sedation and using imaging guidance in a fully equipped interventional or procedure room. Patients will be medically cleared by the anesthesiologist prior to the procedure. Following the procedure, patients will be monitored for at least 24 hours in an inpatient setting until fully recovered, prior to being discharged from the clinic after completion of the visit assessments. A follow-up safety MRI

will be performed approximately 1 month after the procedure to monitor for any subclinical neurological signs.

#### **6.2.2.4 Risks Associated with AAV9-Based Therapy**

The viral capsid of AAV9 may trigger the innate and adaptive immune system. Overall, products (investigational and marketed) using the AAV9 vector have been safe and generally well tolerated in over 500 patients. Out of an estimated 21 clinical trials investigating AAV9-based gene therapies, 7 use an IT route of administration with approximately 60 patients having received an investigational therapy. The mode of administration via CSF is intended to minimize systemic exposure, but inevitably there will be some escape of virus out of the CSF into the blood. In clinical studies, gene therapy candidates using AAV9 have been generally well tolerated. Transient elevations in AST and/or ALT, which respond to corticosteroid treatment, have been reported ([Mendell et al 2017](#)).

Pleocytosis and increased protein in the CSF was observed in one patient dosed with PR001A (Prevail's AAV9-based gene therapy candidate delivering the GBA1 gene to subjects suffering from PD-GBA). Steroid-responsive CSF pleocytosis has been reported in another gene therapy trial utilizing AAV9 viral vector to deliver GAN gene to the patients suffering from giant axonal neuropathy (NCT02362438) ([Bharucha-Goebel et al, 2020](#)).

To mitigate the risk of potential capsid and other related immune reactions, the prophylactic course of immunosuppressive treatment (consisting of corticosteroids and sirolimus) should be followed as specified in the protocol. In cases of elevations of liver enzymes, inflammatory changes in the CSF or other suspected immune reactions to PR006A, higher doses, prolongation or re-initiation of immunosuppressive treatment may be considered at the discretion of the principal investigator. Risk mitigation for the immunosuppressive regimen is discussed in [Section 6.2.2.2](#).

While minimal axonal degeneration and gliosis limited to the dorsal funiculus as well as minimally increased cellularity in small clusters occurred in the DRG of few PR006A-treated NHPs, these findings were non-inflammatory, limited in their extent, and without clinical correlate, and therefore deemed non-adverse (PRV-2018-028). It is not predicted that the non-adverse findings in the NHPs will clinically translate to human patients. Notwithstanding, the protocol will exclude individuals with clinical evidence of peripheral symmetric sensory polyneuropathy and incidence of sensory symptoms will be monitored

during the study using the TNAS. If sensory symptoms appear after PR006A dosing, consultation with a neurologist with expertise in peripheral nerve disease should be considered along with additional corticosteroid use and or prolongation of prednisone or sirolimus taper.

### 6.2.2.5 Risks Associated with *GRN* Expression

There has been no previous experience with administration of a vector in humans aimed at expression of *GRN*. Since FTD-GRN patients are heterozygous mutation carriers and express a certain amount of normal PGRN, the potential risk to develop an immune response to the “wild type” PGRN produced by the transduced cells may be considered as null. In addition, prophylactic corticosteroids will be administered to mitigate the risk of an immune response.

Progranulin is a secreted glycoprotein associated with the regulation of lysosome function and inflammation ([Chitramuthu et al 2017](#)). Progranulin is broadly expressed in the CNS and periphery in a variety of cell types ([Chitramuthu et al 2017](#)). Progranulin expression has been reported to be upregulated in certain tumors and tumor cell lines ([Serrero 2003](#); [Chitramuthu et al 2017](#)). Furthermore, overexpression of PGRN in vitro, in tumor cell lines or primary tumor cells, has been reported to increase certain tumorigenic properties in some contexts ([He et al 2002](#); [Chitramuthu et al 2017](#)) but not in other contexts ([Matsumura et al 2006](#)). In contrast to these studies, overexpression of PGRN in vivo has been reported by several groups using AAV or lentiviral transduction and transgenic mouse approaches, without findings of tumor formation ([Tao et al 2012](#); [Altmann et al 2016](#); [Arrant et al 2018](#)). Furthermore, direct intravenous administration of PGRN in vivo has not been reported to be associated with tumorigenesis ([Tang et al 2011](#)). Consistent with these findings, the Sponsor’s in vivo studies using PR006A to overexpress PGRN in mouse models or normal NHPs have not revealed tumorigenic potential.

Based on the above analysis, an increased risk of malignancy is considered by the Sponsor to be unlikely in the context of PR006A administration. Patients with a history of cancer within 5 years of Screening or current presence of pre-cancerous lesions will be excluded from study participation, with the exception of fully excised prostate carcinoma in situ and fully excised nonmelanoma skin cancers that have been stable for at least 6 months. Patients will also be required to have up to date age- and gender-appropriate cancer screenings, completed as per the Investigator’s judgment and local standard of care, prior to inclusion/exclusion screening. Additionally, the occurrence of malignancy at any point after gene transfer that is

judged as at least probably related to PR006A per the Sponsor's final causality assessment is one of the study stopping rules ([Section 4.2.4](#)).

#### **6.2.2.6 Risks Associated with the Presence of Antibodies to AAV9**

No known safety risks have been described in patients seropositive to AAV9; however, in case of the presence of antibodies to AAV9, there is a risk of reduced efficacy of AAV9-based gene therapy. This risk is mitigated by the ICM route of administration of PR006A. Baseline titers of AAV9 antibodies will be assessed in study patients; however, seropositive patients will not be screen failed.

#### **6.2.2.7 Risks Associated with Other Study Procedures**

The risks associated with other study procedures, including MRA, MRI, general anesthesia or deep sedation, and blood sample collection are described in the ICF.

### **6.3 Safety Monitoring Committee**

The safety of the study will be monitored by an iDMC, as described in [Section 11.1.1](#).

### **6.4 Pregnancy**

Pregnancy is not regarded as an AE unless there is a suspicion that the investigational product may have interfered with the effectiveness of a contraceptive medication. Any pregnancy that occurs during study participation must be reported using the same procedures as an SAE ([Section 6.2.1.6](#)). To ensure patient safety, each pregnancy must be reported within 24 hours of learning of its occurrence. The Investigator will continue to follow patients (or partners of male patients) who become pregnant under the current protocol and will collect information on the pregnancy complications as well as on potential birth abnormalities and/or defects (including spontaneous miscarriage, elective termination, normal birth, or congenital abnormality) and status of mother and child, even if the patient discontinued from the study. Pregnancy complications and elective terminations for medical reasons should be reported as an AE or SAE. Spontaneous miscarriages must be reported as an SAE.

Any SAE occurring in association with a pregnancy, brought to the Investigator's attention after the patient has completed the study, and considered by the Investigator as possibly related to the study treatment must be promptly reported.

## 6.5 Laboratory Analyses

The laboratory parameters will be tested per the Schedules of Events ([Table 13-1](#) and [Table 13-2](#)):

### ***GRN* Sequencing**

At Screening, patients that meet all criteria will be tested for full *GRN* sequencing by the central laboratory. Documentation of prior testing demonstrating the presence of at least 1 pathogenic *GRN* mutation from a Clinical Laboratory Improvement Amendments (CLIA)-approved laboratory or an ex-US CLIA-equivalent certified laboratory that is verified by the Investigator is allowed so the patient can continue Screening without waiting for central laboratory results. However, central laboratory confirmation of *GRN* is required prior to investigational product administration. Results from the external laboratory should be filed in the patient's medical record.

### **Standard Safety Chemistry Panel**

|                            |                                      |
|----------------------------|--------------------------------------|
| Alanine aminotransferase   | Albumin                              |
| Alkaline phosphatase       | Amylase                              |
| Aspartate aminotransferase | Bicarbonate                          |
| Blood urea nitrogen        | Calcium                              |
| Chloride                   | Creatine kinase                      |
| Creatinine                 | Estimated glomerular filtration rate |
| Gamma-glutamyl transferase | Glucose                              |
| Inorganic phosphorus       | Lactate dehydrogenase                |
| Lipase                     | Potassium                            |
| Sodium                     | Total bilirubin                      |
| Total protein              | Uric acid                            |

1. During Screening and until the end of the corticosteroid taper, blood chemistry will be performed fasting.

**Additional Chemistry Parameters**

|                                                                                                                                 |              |
|---------------------------------------------------------------------------------------------------------------------------------|--------------|
| HbA1c                                                                                                                           | Fructosamine |
| Lipid panel (total cholesterol, high-density lipoprotein cholesterol, low-density lipoprotein cholesterol, total triglycerides) |              |

1. During Screening and until the end of the corticosteroid taper, blood chemistry will be performed fasting.

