##### **3.1.1 Year 1**

Fifteen patients will be administered a one-time dose of PR006A, suboccipitally injected into the cisterna magna by an interventional radiologist or neurosurgeon.

In each cohort, enrollment will be staggered by at least 8 weeks between the first 2 patients and then an additional 8 weeks between the second patient and the remaining 3 patients of the cohort to permit review of safety, tolerability, immunogenicity, and, to the extent available, efficacy by the iDMC, who will ultimately provide a recommendation on further dosing. At least 8 weeks after the second staggered patient is dosed in Cohort 1, the iDMC will review all available safety, tolerability, immunogenicity, and, to the extent feasible, efficacy results from the first 2 patients in this cohort (dosed in a staggered manner). At the recommendation of the iDMC, the Sponsor will decide whether to dose the remaining 3 patients in Cohort 1 (low dose) without staggering and in parallel begin staggered enrollment in the mid-dose cohort (Cohort 2).

Cohort 2 will enroll 5 patients to receive the mid-dose ( $7.0 \times 10^{13}$  vg) of PR006A, and

[REDACTED]. The design for Cohorts 2 [REDACTED] enrollment is the same as for Cohort 1.

If a decision is made to not open or to limit enrollment into a cohort (i.e., Cohort 2 and/or [REDACTED] due to safety or tolerability reasons, the unenrolled subjects may be re-allocated to a lower dose level cohort.

One loading dose of 6 mg oral sirolimus will be administered at Day -1, as well as a single dose of 1 g IV methylprednisone at Day 0. A concomitant maintenance dose of 2 mg/day sirolimus will be administered orally for 90 days starting at Day 0 which will then be tapered over the ensuing 15 to 30 days. The maintenance dose is administered to achieve a trough sirolimus concentration of 4 ng/mL (range 2 to 8 ng/mL). One day after treatment with PR006A, patients will start prednisone 30 mg orally for 14 days, followed by a 7-day taper. At the Investigator's discretion, adjustments of dose and duration are permitted.

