## **5.5 Investigational Product Administration**

### **5.5.1 Immunosuppressant Administration**

#### **5.5.1.1 Corticosteroid Administration**

Subjects will receive a loading dose of methylprednisolone 1 g IV pulse on Day 0. Prednisone at a dose of 30 mg/day will be given orally as concomitant medication from Day 1 for 14 days, which will be then tapered over the ensuing 7 days. At the Investigator's discretion, higher doses or a longer taper of corticosteroids may be used.

Mitigation of risks associated with use of corticosteroids, including monitoring for AEs that may be related to corticosteroid use are described in [Section 6.2.2.2](#).

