#### **5.5.1.3 Immunosuppression Monitoring Criteria**

In addition to monitoring sirolimus trough levels, the Investigator should evaluate patient's clinical status, lab findings and potential AEs.

Consideration should also be given to the need to increase doses of the immunosuppressant agent, prolong the tapering regimen, add a third agent or re-initiate treatment based on clinical signs or symptoms consistent with an immune response, including:

- Asymptomatic pleocytosis with WBC > 30 mm^3 and/or high CSF protein (> 70 mg/dL)

- CSF pleocytosis and/or increased protein accompanied by clinical symptoms (including decompensation of underlying FTD symptoms)
- Emergence of sensory symptoms based on neurological examination and/or TNAS.
- ALT and/or AST elevation  $>5 \times$  ULN in conjunction with hepatitis symptoms (e.g., jaundice, fatigue)
- ALT and/or AST elevation  $>10 \times$  ULN irrespective of the presence or absence of clinical symptomatology

The Investigator should consider implementing a longer prednisone taper over an additional 4 weeks in patients presenting with ALT and/or AST  $>3 \times$  ULN at the end of the initial 14-day taper. In case of AST/ALT elevations refractory to prednisone treatment, the Investigator should seek expert advice from a hepatologist.

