#### **6.2.2.2 Risks Associated with the Use of Immunosuppressants**

One loading dose of 6 mg oral sirolimus will be administered at Day -1, as well as a single dose of 1 g IV methylprednisone at Day 0. A concomitant maintenance dose of 2 mg/day sirolimus will be administered orally for 90 days starting at Day 0 which will then be tapered over the ensuing 15 to 30 days. The maintenance dose is administered to achieve trough sirolimus concentration of 4 ng/mL (range 2 to 8 ng/mL). One day after treatment with PR006A, patients will start prednisone 30 mg orally for 14 days, followed by a 7-day taper. At the Investigator's discretion, adjustments of dose and duration are permitted.

Corticosteroids are administered for prophylactic suppression of inflammatory responses and to improve viral transduction. Despite the beneficial effects of prednisone and sirolimus in the prevention and management of potential liver enzyme abnormalities, systemic immunosuppressants in this dose range can produce a variety of AEs ranging from mild irritability to life-threatening or even fatal biochemical effects including but not limited to impaired wound healing, interstitial lung disease, hyperglycemia, hypertension, lymphomas/malignancies, hyperlipidemia, decline in renal function, proteinuria, embryo-fetal toxicity, and male fertility. While patients will be excluded if they are at increased risk of AEs, if corticosteroid side effects emerge, corticosteroids will be stopped or tapered as medically indicated. Glucose level checks, HbA1c, fructosamine, blood pressure, body weight, cholesterol, urine protein, lipids, red blood cell counts, neutrophil counts, protein glucose, CSF cell counts, CSF protein levels, CSF glucose levels, sirolimus trough concentrations, BMI, waist circumference, and psychosis incidence/aggravation will be monitored at study visits occurring during corticosteroid usage and after prednisone

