### **7.1 Primary Endpoints**

#### **7.1.1 Primary Safety Endpoints**

The following primary safety endpoints are measured up to 5 years:

- Incidence and severity of TEAEs and SAEs, including clinically significant changes in vital signs, clinical laboratory assessments, C-SSRS, and TNAS; treatment-emergent transaminitis; treatment-emergent diabetes and prediabetes; treatment-emergent peptic ulcer disease and/or erosive gastritis; treatment-emergent osteoporosis; treatment-emergent increase in body weight  $\geq 5\%$  from baseline, treatment-emergent BMI  $>25$  or  $>30$ , and treatment-emergent increase in waist circumference  $\geq 15\%$  from baseline; incidence of Grade  $\geq 3$  infections; incidence/aggravation of psychosis; treatment-emergent hypercholesterolemia or hyperlipidemia; treatment-emergent interstitial lung disease; treatment-emergent opportunistic infections (including progressive multifocal leukoencephalopathy (PML) and BK virus-associated nephropathy); sirolimus trough levels; 12-lead ECGs; brain MRIs; physical examinations; and neurological examinations
- Sum of ARs and suspected ARs
- Sum of serious ARs and serious suspected ARs
- Incidence of procedure or treatment-emergent safety findings as per brain MRI.
- Change from baseline in immunogenicity of AAV9 and PGRN in blood at Day 14 and Months 1, 2, 3, 6, 9, and 12 and in CSF at Months 2 and 12.

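### Required fasting for blood chemistry ends with the prednisone taper (nominally Day 21) while sirolimus continues to about Day 105–120, so triglycerides and glucose at Months 1–3 may be compared with a fasting baseline under a different sampling condition

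*Protocol*

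**What the plan says.** The fasting rule appears three times in the protocol in the same words: under the standard safety chemistry panel (which contains glucose) and the additional chemistry parameters (which contain the lipid panel) in Section 6.5, and as footnote r of Table 13-1. It reads: "During Screening and until the end of the corticosteroid taper, blood chemistry will be performed fasting". No other place in the protocol requires fasting, and the chemistry and lipid rows of Table 13-2 carry no such footnote.

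Section 5.5.1.1 gives oral prednisone "from Day 1 for 14 days, which will be then tapered over the ensuing 7 days". It adds that, at the Investigator's discretion, "higher doses or a longer taper of corticosteroids may be used", and Section 5.5.1.3 describes a "longer prednisone taper over an additional 4 weeks" for raised liver enzymes.

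Sirolimus lasts longer. Section 6.2.2.2 has it "administered orally for 90 days starting at Day 0 which will then be tapered over the ensuing 15 to 30 days". Sections 1.3 and 6.2.2.2 name hyperlipidemia among its risks. The primary safety endpoints in Section 7.1.1, measured up to 5 years, include "treatment-emergent hypercholesterolemia or hyperlipidemia" and treatment-emergent diabetes and prediabetes.

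**The concern.** The fasting requirement follows the shorter of the two immunosuppressant courses, while the lipid risk and the endpoint that captures it outlast that course. A treatment-emergent lipid or glucose abnormality is naturally judged against the pre-dose value, which is a required fasting sample. Once the requirement lapses, a later rise can come from the drug, from a meal, or from both.

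Two features make this matter more here. There is no control arm to show how far values move for reasons other than treatment. And, under Sections 1.2.3 and 3.1.1, escalation rests on data through Month 2 in as few as two patients, with the iDMC assessing the primary safety variables. Month 2 is a visit at which fasting is nominally not required, so one ambiguous value carries weight.

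**Working it through.** The protocol states no figure to reproduce; the check is one of dates and visits.

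**Inputs**
- Prednisone: 14 days from Day 1, then a 7-day taper (Section 5.5.1.1).
- Sirolimus: 90 days from Day 0, then 15 to 30 days of taper (Sections 3.1.1 and 6.2.2.2).
- Chemistry with lipids after dosing: Days 7, 14, 21 and Months 1, 2, 3, 6, 9, 12 (Table 13-1); Months 18, 24, 30, 36, 42, 48, 54, 60 (Table 13-2).
- Windows: Day 21 ±2 days, Month 1 ±7, Month 2 +14, Month 3 ±7.

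**Dates**
- Nominal end of prednisone taper: 14 + 7 = Day 21.
- End of sirolimus taper: 90 + 15 = Day 105 to 90 + 30 = Day 120.
- Time on sirolimus without required fasting: 90 − 21 = 69 maintenance days, or 105 − 21 = 84 to 120 − 21 = 99 days counting the taper.

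**Visits in the sirolimus period** (taking a month as 30.4 days)

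| Visit | Day (window) | Fasting required? |
|---|---|---|
| Day 7 | 7 (6–8) | Yes |
| Day 14 | 14 (12–16) | Yes |
| Day 21 | 21 (19–23) | Yes, unless the visit falls after the taper |
| Month 1 | 30 (23–37) | No; yes if the prednisone taper is extended |
| Month 2 | 61 (61–75) | No |
| Month 3 | 91 (84–98) | No |

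A four-week extension ends on Day 21 + 28 = Day 49. That covers Month 1 but not Month 2. Only a still longer course would reach Months 2 or 3. The required condition at Month 1 can therefore differ between patients of the same cohort. Section 5.5.1.3 also describes the initial taper as lasting 14 days, against 7 days in Section 5.5.1.1; the two must be reconciled, because the fasting rule hangs on that date.

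**All visits.** There are 9 + 8 = 17 post-dose draws. On the nominal schedule 3 are under the fasting rule and 14 are not. Of those 14, 11 (Months 6, 9, 12 and the eight follow-up visits) come after sirolimus has ended, which leaves three that bear on sirolimus.

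**Glycaemia.** Table 13-1 schedules HbA1c at Screening, Day −1 and Months 2 and 3, and fructosamine at Day −1 and Day 7. Table 13-2 has neither. After Month 3, apart from unscheduled tests and the end-of-therapy HbA1c for patients on prednisone for more than 3 months, glucose is the only scheduled blood measure of glycaemia.

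**Direction of the effect, on assumed figures.** Suppose fasting triglycerides have mean 120 and SD 40 mg/dL, the limit is 150, there is no drug effect, and every later sample is fed, adding 20 to 40 mg/dL. The share above the limit is:
- fasting: P(Z > (150 − 120)/40) = P(Z > 0.75) = 0.227;
- fed, +20: P(Z > 0.25) = 0.401;
- fed, +40: P(Z > −0.25) = 0.599.

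With otherwise stable values, new crossings among 15 patients would be 15 × (0.401 − 0.227) = 2.6 to 15 × (0.599 − 0.227) = 5.6. None of these inputs is in the protocol, and a crossing is not an adverse event. The figures show direction only.

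**The case against.** The strongest reply is that the protocol already filters such values. Under Section 6.5 an abnormal result becomes an adverse event only if the Investigator judges it clinically significant, and unexplained clinically significant values after dosing are to be repeated and followed until normal or explained. This stands against anyone who infers that fed samples will automatically generate false events for the iDMC. It does not make the values comparable: the repeat is not specified as fasting, the protocol does not call for fasting status to be recorded, and summaries of change from baseline use the values as drawn.

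A reader might also infer from 14 uncovered draws out of 17 that a sirolimus effect on lipids can never be separated from meal state. The protocol does not support that. Eleven of the 14 draws fall after sirolimus, and Days 7, 14 and 21 are on sirolimus and under the fasting rule.

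Four further limits stand:
- Not requiring fasting is not the same as patients being fed. Study manuals, which are not shown, could add instructions.
- HbA1c at Months 2 and 3 partly covers glycaemia in the sirolimus period.
- As general laboratory knowledge rather than anything in the protocol, triglycerides and glucose depend on meals most, total and HDL cholesterol less, and HbA1c not.
- Uncontrolled hyperlipidemia is an exclusion, so the triglyceride illustration may not describe the enrolled population.

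Finally, mandatory fasting at every visit for five years would burden patients with dementia. The recommended sequence places rating scales before blood sampling, so those scales would then be done fasting. That is a fair objection to a five-year fasting rule, but not to one limited to the sirolimus period.

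**Conclusion.** The point holds in a limited form. The fasting rule stops nominally at Day 21, while sirolimus runs to about Day 105–120. Fasting is not required at Months 2 and 3 on the nominal schedule or with the four-week extension that the protocol describes, nor at Month 1 unless the taper is extended. The affected measures are chiefly triglycerides, and also glucose. After Month 3 the issue is interpretability: scheduled glucose is then the only routine blood measure of glycaemia, and its fasting state is unspecified.

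The conclusion rests on the protocol text alone, on a treatment-emergent finding being judged against the pre-dose fasting value (implied rather than spelled out), and on triglycerides and glucose responding to meals, which the protocol's own fasting rule presupposes. The size of any distortion cannot be estimated from the protocol. This is an inexpensive improvement to a primary safety component; it does not show that the safety evaluation fails.

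**What to change.** 1. Reword footnote 1 under both chemistry tables in Section 6.5, and footnote r of Table 13-1, along these lines: *Blood chemistry and lipid panel samples will be collected fasting at Screening, Day −1 and all visits through the end of the sirolimus taper (at least through Month 3).* This also frees the rule from the date on which an individual prednisone taper ends.
2. Record fasting status (yes/no) at every chemistry or lipid draw, including unscheduled draws and the Table 13-2 visits, so that later non-fasting triglyceride and glucose values can be identified. If it is not recorded, no analysis can recover it.
3. Reconcile the two descriptions of the initial prednisone taper in Sections 5.5.1.1 and 5.5.1.3.

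The cost is fasting before about three more visits (Months 1, 2 and 3) and one added data field. At those visits patients already attend before their sirolimus dose for trough sampling. No sample, visit or treatment changes. Fasting throughout the five years is not needed to meet the point.
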